In addition, we will monitor rates of appendiceal perforation, negative appendectomies, and missed appendicitis in our study cohort to ensure the safety of our proposed intervention. This innovative project builds on extensive previous work by our interdisciplinary team, including derivation and validation of pediatric ED clinical decision rules, CDS development and implementation, and economic and statistical analyses of ED resource use. The proposed point-of-care CDS tool will be a scalable model for using EHR-linked, web-based technology to safely deliver personalized and evidence-based care for children in the ED.

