#### d) Preliminary Studies

**Pilot data:** We recently completed a single-center pilot study to implement CDS integrated in an EHR for pediatric patients with acute abdominal pain. For this project, based in the 2 primary EDs of Children's Hospitals and Clinics of Minnesota (Children's Hospital), we engaged a multidisciplinary team of radiologists, surgeons, and ED physicians to develop a consensus care pathway. Similar to the current proposal, goals of the pilot were to reduce CT use among pediatric patients with ED visits for acute abdominal pain. The pilot CDS stratified patients into 3 risk groups based on previously validated decision rules. First, we identified pediatric patients with acute abdominal pain at low risk for appendicitis who could safely forgo CT by applying our previously derived and validated decision rule. Patients with an ANC  $<6.75 \times 10^3/\mu\text{L}$ , absence of nausea, and absence of maximal tenderness in the right lower quadrant were identified as at low risk for appendicitis. Second, to determine which patients were at high risk for appendicitis and could proceed to the operating room without imaging, we used the externally validated Pediatric Appendicitis Score (PAS). The remaining patients were classified as medium risk, and ultrasound was the recommended initial imaging modality. We then worked with our informatics group to create a simple "time-of-ordering alert": the pilot CDS tool was presented to clinicians when ordering a CT or ultrasound for patients with acute abdominal pain. The CDS tool was modified and refined in two phases. Drs. [name] and [name], members of the Clinical Advisory Council for the current proposal, were instrumental to the success of the pilot.

Over the 36-month study period, 4,234 pediatric and adolescent patients with acute abdominal pain received care in the pilot EDs. Of these, 778 (18%) had appendicitis and 178 (23% of appendicitis cases) had a perforated appendix. After CDS was implemented, 942 (22%) had an abdominal CT, and 1,666 (39%) had an ultrasound. Interrupted time series design revealed a significant 23% decline in CT use post-implementation ( $OR=0.77$  (95%CI.67-.88)  $P<0.01$ ) (Figure 1). Safety outcomes remained unchanged over the study period.

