### Identification of a cohort of patients with acute abdominal pain at risk for appendicitis (Hypothesis 1):

Using existing EHR data and simple prompts implemented at triage at all 17 sites over the 6-month pre-intervention period and 24-month trial we will identify our study cohort of children and adolescents at elevated risk for appendicitis. The algorithm underlying this tool will exclude patients with chronic abdominal pain, abdominal trauma, and/or pregnancy, because their management is beyond the scope of the proposed intervention. For patients undergoing an appendectomy within 7 days of their index ED visit, a trained, blinded nurse abstractor will review their pathology report. For patients undergoing appendectomy, appendicitis is defined by specific terminology on the pathology report, as in our previous multicenter study (consistent with appendicitis, neutrophil invasion of tissue, serosal inflammation, acute peri-appendicitis, or acute appendicitis). For patients with perforation undergoing drainage and/or intravenous antibiotics and interval appendectomy, diagnosis will be based on clinical notes from the treating surgeon. For patients transferred from the ED where they initially sought care to a facility with pediatric surgical expertise, we will seek final diagnoses and pathology reports from the receiving institution. If we are unable to verify final diagnosis, the patient will be excluded from primary analyses. These patients may be included sensitivity analyses with the diagnosis of appendicitis or not appendicitis assigned based on provider impression and imaging available at the time of ED discharge / transfer. For HPMG, outside of the study EDs, Children's Hospital would be the primary outside institution to receive transfers for further evaluation and appendectomy. Thus, we will establish a registry of patients with a discharge diagnosis of appendicitis from Children's Hospital and use a probabilistic method to determine whether these patients are matches with patients receiving care in the HPMG study EDs. KPNC uses a hub and spoke system for pediatric surgery. Among the 11 CREST sites are four pediatric surgical hubs.

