**Appendiceal perforation, negative appendectomies, and missed appendicitis** (safety outcomes): Although it is unlikely that the Appy-CDS will significantly increase rates of adverse events, the following clinical or safety outcomes will be monitored both before and during the full Appy-CDS intervention. *Appendiceal perforation* will be evaluated in patients who undergo appendectomy based on chart review of the surgeon's intra-operative note. As in our previous work, perforation will be defined by keywords in the operative report (presence of abscess, peritonitis, complex appendicitis, or purulent material). In addition, we will review all charts for patients with a discharge diagnosis of perforated appendicitis (ICD-9 540.1) who do not undergo an appendectomy during their index hospitalization, because a subset of patients with appendiceal perforation (4% in our previous multicenter cohort, unpublished data) will be admitted for intravenous antibiotics and undergo an interval appendectomy 6-12 months later. *Negative appendectomies* are appendectomies in which the pathology report reveals no evidence of appendiceal inflammation. This will be determined via review of pathology reports. *Missed appendicitis* is when a patient presents for the evaluation of abdominal pain, is discharged home, and returns within 1 week with appendicitis. Missed appendicitis will be identified through review of automated EHR data for all patients with appendicitis. As described above, under exclusion criteria, patients who are transferred for definitive care and whose final pathology and surgical reports are not available will not be included in the assessment of safety outcomes.

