**Table 4. Appendicitis Specific Outcomes**

| Condition               | Description                                                                                                                                                                          | How outcome will be identified                                                                                                                                                                                                                                                                                                                                                                                                                                                                                                                   |
|-------------------------|--------------------------------------------------------------------------------------------------------------------------------------------------------------------------------------|--------------------------------------------------------------------------------------------------------------------------------------------------------------------------------------------------------------------------------------------------------------------------------------------------------------------------------------------------------------------------------------------------------------------------------------------------------------------------------------------------------------------------------------------------|
| Appendiceal perforation | Appendicitis with perforation of the appendix, resulting in purulent material in the peritoneal cavity; can include abscess formation                                                | 
 
1. Chart review of surgeon's operative note; Key terms "presence of abscess", "peritonitis", "complex appendicitis", "purulent material" "ruptured appendix", or "likely perforated appendicitis"
 
2. ICD-10 for appendicitis with local or generalized peritonitis (K35.2, K35.3) with hospitalization for intravenous antibiotics who do not undergo appendectomy on initial hospitalization
 
3. We will report appendiceal perforation rates, among those with appendicitis
 
 |

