**Table 6. Missed Care for Other Abdominal Emergencies**

| Condition                                      | Description                                                                                        | How outcome will be identified                                                                                                                                                                                                      |
|------------------------------------------------|----------------------------------------------------------------------------------------------------|-------------------------------------------------------------------------------------------------------------------------------------------------------------------------------------------------------------------------------------|
| Medical emergencies that require intervention  | Small bowel obstruction, tub-ovarian abscess, pelvic inflammatory disease, pyelonephritis          | 1. Diagnoses within 7 days of index ED visit will be identified from EHR and billing records via ICD-10 codes
2. Potential cases will be manually reviewed by site PIs to determine whether there was a delay in definitive care |
| Surgical emergencies that require intervention | ovarian torsion; testicular torsion, abdominal tumor, intussusception, volvulus, ectopic pregnancy | 1. Diagnoses within 7 days of index ED visit will be identified from EHR and billing records via ICD-10 codes
2. Potential cases will be manually reviewed by site PIs to determine whether there was a delay in definitive care |

Safety outcome rates for intervention and control EDs will be reported to the IDMC every 6 months throughout the 2 year cluster randomized trial. Eligibility and enrollment will also be tracked and reported to the IDMC every 6 months, starting in the pre-intervention period. An example of the enrollment table is shown below (Table 7).

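### Perforation is reported by arm only among children with appendicitis, a diagnosis the intervention could influence; show it per patient as well and define the denominator

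*Combined protocol and SAP*

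**What the plan says.** Table 4 (section 9) fixes the form of the perforation outcome: "We will report appendiceal perforation rates, among those with appendicitis". The text after Table 6 makes it a between-arm report: "Safety outcome rates for intervention and control EDs will be reported to the IDMC every 6 months". The Background is looser and names no denominator: "we will monitor rates of appendiceal perforation, negative appendectomies, and missed appendicitis in our study cohort".

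Section 6b (Hypothesis 1 cohort) describes how appendicitis is established in two groups. For operated children: "For patients undergoing appendectomy, appendicitis is defined by specific terminology on the pathology report". For one unoperated group: "For patients with perforation undergoing drainage and/or intravenous antibiotics and interval appendectomy, diagnosis will be based on clinical notes from the treating surgeon". Table 4 adds unoperated children to the perforation count through the ICD-10 peritonitis codes, "with hospitalization for intravenous antibiotics who do not undergo appendectomy on initial hospitalization". The safety paragraph of section 6b explains why: "a subset of patients with appendiceal perforation (4% in our previous multicenter cohort, unpublished data) will be admitted for intravenous antibiotics".

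Neither place says what happens to a child with unperforated appendicitis treated without surgery, and Table 4 does not say which record establishes membership of its denominator. Children transferred out whose operative and pathology notes cannot be obtained leave the safety analyses (section 3a).

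**The concern.** A comparison between arms is protected by randomisation only if the group compared is not shaped by the intervention. Appendicitis is established after randomisation. The recommendation tables in Appendices A and B direct low-risk children toward no imaging and outpatient follow-up, so the intervention could change how many mild cases are diagnosed.

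Fewer mild diagnoses shrink the denominator and raise the perforation proportion with no additional perforation. More mild diagnoses can hide a real rise. An appendicitis definition that captured unoperated cases more readily when perforated than when not would add a second way for the denominator to shift.

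At stake is what the monitoring committee sees. The Dissemination section calls the safety outcomes particularly important because clinicians may hesitate to discharge a child without a negative CT. A proportion that can mislead in either direction is a weak basis for reassurance or alarm.

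**Working it through.** **Plan's own figures.** The pilot (section 2d) states: "Of these, 778 (18%) had appendicitis and 178 (23% of appendicitis cases) had a perforated appendix". Check: 178/778 = 22.9% and 778/4,234 = 18.4%, matching the stated 23% and 18%. The pilot percentage is built the same way as the Table 4 rate.

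**Inputs for the illustration**
- Cohort: 4,200 at-risk patients per year over 14 EDs (Sample size and power), 24 months (section 3), two arms assumed equal: 4,200 × 2 / 2 = 4,200 per arm.
- Appendicitis: 20%, the target positive predictive value (Hypothesis 1): 840 cases. As a plausibility check, the forecast 2,634 cases over 4,200 × 3 = 12,600 at-risk patients is 20.9%.
- Perforated: 23% as in the pilot: 840 × 0.23 = 193.2. Unperforated: 840 − 193.2 = 646.8.
- Shares lost or gained: assumed. The documents give none.

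**Fewer unperforated cases counted in one arm, perforations unchanged**
- 5% fewer: 193.2 / (840 − 32.3) = 193.2/807.7 = 23.9%
- 10% fewer: 193.2 / (840 − 64.7) = 193.2/775.3 = 24.9%
- 15% fewer: 193.2 / (840 − 97.0) = 193.2/743.0 = 26.0%

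Per 1,000 enrolled, each case reads 193.2/4.2 = 46.0. The same arithmetic applies whether the missing cases were never diagnosed or were treated without surgery and not counted.

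**A rise that does not show.** With 10% more perforated and 10% more unperforated cases, the proportion is 212.5/924 = 23.0%, unchanged. Per 1,000 enrolled it is 212.5/4.2 = 50.6 against 46.0.

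**Sampling error.** The 95% half-width for the arm difference, ignoring clustering, is 1.96 × √(2 × 0.23 × 0.77 / 840) = 4.0 points at the end. For one six-month interval (840/4 = 210 cases per arm) it is 1.96 × √(2 × 0.23 × 0.77 / 210) = 8.0 points.

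**How firm is an enrolled denominator?** Enrolment requires completed screening questions. In the Appendix C example (one HealthPartners site, November 2016 to April 2017), patients reaching the screening step number 64 + 43 + 54 + 53 + 45 + 55 = 314. Screening was not completed for 37 + 10 + 15 + 23 + 18 + 27 = 130, or 41%. If one arm enrolled 10% more children, none with a perforation (assumed), the same 193.2 perforations would read 193.2/4.62 = 41.8 per 1,000 instead of 46.0.

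**The case against.** The case against has real force.

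- **Size.** Shifts of 0.9 to 3.0 points sit inside a 4-point half-width at the end and an 8-point one for a single six-month interval. The documents show no difference between arms in diagnosis or non-operative treatment, and they plan no formal test of perforation. This stands, and it limits the point to an improvement in reporting.
- **Narrow route.** The HealthPartners chart form asks about appendicitis up to day 7, so a mild case that returns within a week can still be counted, and missed appendicitis is reported separately. The masking example needs more mild diagnoses, which is not what fewer scans would suggest. This also stands: both scenarios are illustrations. Separate reporting of missed appendicitis and negative appendectomy helps, but neither gives perforations per child seen.
- **Case definition.** A reader might infer that unoperated children count only if perforated. The documents do not say so. Section 6b is silent on unperforated, unoperated cases, and several records can hold them: the diagnosis item on the HealthPartners form (separate from the appendectomy item), the final-diagnosis item on the Children's form, the appendicitis diagnosis variable in the Hypothesis 1 dictionary, and the non-perforated discharge diagnosis in the Hypothesis 2 dictionary. What stands is that none of these is named as the source of the Table 4 denominator.
- **Replacement denominator.** A reader might conclude that a per-enrolled rate should replace the conditional one. It should not stand alone. Enrolment is also determined after randomisation through screening completion, which at Kaiser requires the provider to open RISTRA.

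**Conclusion.** The point holds as a vulnerability in how one safety outcome is reported. The only denominator the plan commits to for perforation is a post-randomisation diagnosis that the intervention could influence, and no rate on a denominator free of that diagnosis is specified.

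Under the assumed planning figures, a 5-15% shortfall of unperforated cases in one arm moves the rate from 23.0% to 23.9-26.0%. A parallel 10% rise in both kinds of case leaves it at 23.0% while perforations go from 46.0 to 50.6 per 1,000 enrolled. These movements are smaller than the sampling error of the arm difference.

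The documents do not support saying that the comparison is biased, that the committee would be misled, or that perforation is the leading harm signal. The plan lists three appendicitis safety outcomes without ranking them. The missing definition of the denominator is a gap in its own right, whatever the size of the shifts.

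**What to change.** For each committee report and the final analysis, by arm and period with baseline values:

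1. Keep the proportion among appendicitis cases, and show the perforation count behind it.
2. Beside it, show perforations per 1,000 enrolled patients and per 1,000 potentially eligible patients before the screening questions (Column A of the enrolment report in section 7b). For the latter, add to the numerator the perforations found in the quarterly review of missed-eligible cases described after Table 7.
3. Show screening completion and the number of transfers excluded from the safety analyses.
4. State one appendicitis definition for the conditional rate. It should explicitly include unperforated cases treated without surgery and name the record that establishes them in each health system.

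The cost is a few more table lines and a sentence in the case definition. Enrolment and perforation are already tracked, but the missed-eligible review must also record perforation. The per-patient rates depend on case-mix, and the enrolled one also on screening completion, so none of the three rates should be read alone.

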| Negative appendectomy   | An appendectomy occurring in the setting of acute abdominal pain with normal pathology, no evidence of inflammation, where an appendectomy is the only surgical procedure performed. | 
 
1. Chart review of appendix pathology reports
 
2. Does not include incidental appendectomies, if appendectomy is part of more extensive abdominal procedure
 
                                                                                                                                                                                                                                                                                                                     |
| Missed appendicitis     | A patient who is evaluated in a study ED for acute abdominal pain is discharged home and then returns, within 7 days, with appendicitis                                              | 
 
1. Review of EHR and claims data for ICD-10 codes: K35, K35.2, K35.3, K35.8, K35.89, K36, K37 within 12 days of index ED visit, to account for diagnosis date to be hospital discharge date. Followed by manual review to confirm whether appendicitis was within 7 days of index ED visit.
 
                                                                                                                                                                                                    |

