### Return Visit Information

Did the patient return to Children's within 7 days?

- ☐ Yes  
☐ No

How many times did the patient return to Children's within 7 days? (Do not include a transfer)

- ☐ 1 return visit  
☐ 2 return visits  
☐ 3 return visits  
☐ 4 return visits  
☐ 5 return visits  
☐ 6 return visits  
☐ 7 return visits  
 (This number of visits does not include a transfer to Children's)

---

### Visit 1

Date and time of Children's return visit

\_\_\_\_\_

(MDY H:M)

Where did visit take place?

- ☐ Clinic  
☐ ED  
☐ Inpatient  
☐ ICU  
 (Highest Acuity)

How did the patient arrive at Children's?

- ☐ Car  
☐ EMS  
☐ Public Transportation  
☐ Other

If other, how did the patient arrive?

\_\_\_\_\_

Did the patient have surgery during this visit?

- ☐ Yes  
☐ No

What date and time was the operation?

\_\_\_\_\_

(MDY H:M)

Did the patient have surgery for appendicitis during this visit?

- ☐ Yes  
☐ No

What date and time was the surgery for appendicitis preformed?

\_\_\_\_\_

(MDY H:M)

Was this a negative appendectomy?

(from the pathology report)

☐ Yes

☐ No

(Key Words for Negative Appendectomy: No evidence for neutrophil invasion of tissue, lymphoid hyperplasia present with no evidence for appendicitis, no serosal injection present)

What does pathology report indicate?

Final Diagnosis for this visit

☐ Appendicitis

☐ Perforated Appendicitis (from operative note)

☐ Medical Diagnosis

☐ Other Surgical

(Perforation Key Words: Ruptured appendix, abscess noted in the right lower quadrant, purulent material in abdomen, likely perforated appendicitis, or "complex appendicitis")

What did the operative note indicate?

(Perforation Key Words: Ruptured appendix, abscess noted in the right lower quadrant, purulent material in abdomen, likely perforated appendicitis, or "complex appendicitis")

Did the patient have any of the following surgical emergencies during this visit?

☐ Ovarian torsion

☐ Testicular torsion

☐ Abdominal tumor

☐ Intussusception

☐ Volvulus

☐ Ectopic pregnancy

☐ N/A

(Check all that apply)

Which medical diagnosis

☐ non-specific abdominal Pain

☐ Constipation

☐ Gastritis

☐ Gastroenteritis

☐ Mesenteric Adenitis

☐ PID

☐ Renal Stone

☐ UTI

☐ Other Medical Diagnosis

Did the patient receive imaging at Children's this visit?

☐ Yes

☐ No

What imaging studies did the child receive?

☐ Xray

☐ Ultrasound

☐ CT

☐ MRI

Did one of the following medical emergencies occur?

☐ Small bowel obstruction

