**List of variables for Hypothesis 4.**

| Variable Name  | Variable Type and Length (bytes) | Values                                         | Variable description                                                                                                                                                                                          |
|----------------|----------------------------------|------------------------------------------------|---------------------------------------------------------------------------------------------------------------------------------------------------------------------------------------------------------------|
| Study_ID       | char(7)                          | HP00001, HP00002, etc
KP00001, KP00002, etc | Study id                                                                                                                                                                                                      |
| Pat_Enc_CSN_ID | num(8)                           |                                                | Patient Encounter ID that uniquely identifies an ED visit                                                                                                                                                     |
| Adate          | num(8)                           | sas date/time                                  | Date of diagnosis. This table will include all encounters 30 days after index visit                                                                                                                           |
| Ddate          | num(8)                           | sas date/time                                  |                                                                                                                                                                                                               |
| ENC_TYPE       | num(8)                           | 1=Hospital/ED
2=ICU
3=Clinic/Other       | Designates if the diagnosis was made while in the hospital/ED, ICU. All diagnoses from index visit will have Dx_Hosp_ED='1'. Other diagnoses within 30 days of index visit could have Dx_Hosp_ED= '1' or '2'. |

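### The 12-day code search for missed appendicitis can miss later returns with longer stays that are coded only at discharge, and Table 6 names no date field and gives no allowance

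*Combined protocol and SAP*

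**What the plan says.** Section 9, Table 4 defines missed appendicitis as a patient who "is discharged home and then returns, within 7 days, with appendicitis". Ascertainment has two steps. EHR and claims data are first searched for the listed ICD-10 appendicitis codes "within 12 days of index ED visit, to account for diagnosis date to be hospital discharge date". The second step is given as: "Followed by manual review to confirm whether appendicitis was within 7 days of index ED visit".

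Table 6 covers other missed emergencies, such as torsion, volvulus, small bowel obstruction and ectopic pregnancy. Its first step is: "Diagnoses within 7 days of index ED visit will be identified from EHR and billing records via ICD-10 codes". It does not say which date places a diagnosis inside the window, and it adds no days for discharge dating. Its second step is: "Potential cases will be manually reviewed by site PIs to determine whether there was a delay in definitive care".

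Other parts of the document bear on the same cases:

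- Section 6(b), safety outcomes: "Missed appendicitis will be identified through review of automated EHR data for all patients with appendicitis". No 12-day limit appears there. The same paragraph plans chart review of perforated cases that had no appendectomy at the index hospitalization.
- Section 6(b), Hypothesis 1: an abstractor reads the pathology report of patients who have an appendectomy within 7 days of the index visit.
- Appendix D, Children's form: it asks "Did the patient return to Children's within 7 days" and records each return by visit date, for HealthPartners patients only.
- Appendix E, Hypothesis 4 variables: "This table will include all encounters 30 days after index visit".

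**The concern.** The outcome is defined by when the child comes back, but the search runs on a date that, by the plan's own account, may be when the child leaves hospital. The gap between the two is the length of stay. A fixed allowance therefore finds every short stay and starts to miss cases once stays are long and returns are late. The manual step works only on what the search has found, so it can remove cases but not add them.

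These are safety rates. Table 4 and Table 6 outcomes go to the IDMC every 6 months under a passive surveillance scheme, and Section 8(b) accepts a small chance that the tool increases missed appendicitis. A loss that depends on length of stay is an undesirable property in such a rate.

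**Working it through.** **Inputs.** Outcome window: 7 days (Table 4). Search window: 12 days for appendicitis (Table 4) and 7 days for other emergencies (Table 6). Encounter window in Appendix E, Hypothesis 4: 30 days. Date used: possibly hospital discharge, stated in the Table 4 row only. Expected stay and return-day distribution: not given anywhere. Table 5 defines hospital length of stay but gives no value.

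**The plan's own figure.** 12 = 7 + 5. The 5-day allowance follows by subtraction, but no length of stay is given from which it could be reproduced.

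**Condition for being found.** If the only code is dated at discharge, a return on day d with a stay of L nights falls inside a window of W days when d + L ≤ W. The longest stay still found is W - d.

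| Return day d | W = 12 | W = 7 (if discharge-dated) | W = 30 |
|---|---|---|---|
| 1 | 11 | 6 | 29 |
| 3 | 9 | 4 | 27 |
| 5 | 7 | 2 | 25 |
| 7 | 5 | 0 | 23 |

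A day-7 return staying 6 nights is dated 7 + 6 = 13 and is missed. A day-5 return staying 8 nights is also dated 13 and is missed. A day-1 return staying 11 nights is dated 12 and is found.

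**Share missed at a fixed stay.** Assume d is equally likely to be any of days 1 to 7. The share missed is the number of days with d + L > W, divided by 7.

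- W = 12: L ≤ 5, 0/7 = 0%; L = 6, 1/7 = 14%; L = 7, 2/7 = 29%; L = 8, 3/7 = 43%; L = 10, 5/7 = 71%.
- W = 7, if discharge-dated: L = 0, 0%; L = 1, 1/7 = 14%; L = 2, 2/7 = 29%; L = 3, 3/7 = 43%; L = 5, 5/7 = 71%; L ≥ 7, 100%.
- W = 30: 0% for every stay up to 30 - 7 = 23 nights.

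**Share missed when stays vary.** Assume lognormal stays with log-scale standard deviation 0.6 and a median of 2 to 6 nights. The ranges run from the shortest to the longest median.

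| Return days | W = 12 | W = 7 (if discharge-dated) |
|---|---|---|
| Even over days 1 to 7 | about 2% to 31% | about 34% to 78% |
| Days 1 to 3 only | about 0.3% to 18% | about 5% to 56% |

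These ranges show how far the answer depends on unknown inputs. They do not estimate the trial's loss.

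**The case against.** The strongest reply is that Table 4 already deals with discharge dating. It recognises the issue, adds 5 days and adds a chart check, and no stay of 5 nights or less is lost. A loss needs a longer stay, a late enough return, and no earlier-dated code in the EHR or claims. All of that stands.

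A reader might also infer more than the documents support:

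- **That both searches run on discharge dates.** The plan says so only in the missed-appendicitis row. Table 6 draws on similar records, so the inference is reasonable, but it remains an inference.
- **That the longest stays drop out.** A long stay alone does not lose a case; the sum of return day and stay does.
- **That severe misses are discarded before anyone opens a chart.** Section 6(b) describes EHR review of all patients with appendicitis, chart review of perforated cases without appendectomy, and pathology review of appendectomies within 7 days. Table 4 tracks perforation separately, Table 5 counts ED returns within 7 days, and the Children's form records returns by visit date. Any of these could bring a lost appendicitis case back.
- **That the comparison between arms is biased.** The same search applies to both arms. A differential loss would need the tool to shift misses toward later or longer-stay returns, which is only a possibility.

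The recovery routes weaken the point without closing it. None is tied to the Table 4 count. The pathology review stops at appendectomies by day 7, the Children's form covers HealthPartners patients only, and the Section 6(b) reviews listed concern appendicitis, so they do not ascertain the Table 6 conditions.

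**Conclusion.** The point holds in a limited form. On Table 4's own premise, a qualifying return coded only at discharge falls outside the search when return day plus stay exceeds 12, and the check that follows cannot restore it. No stay of 5 nights or less is affected. Section 6(b) describes ascertainment without the 12-day limit, so the document contains two unreconciled methods for one safety outcome.

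For Table 6, what is established is that the date field is unnamed and no allowance is made. If its codes are discharge-dated too, a day-7 return with any overnight stay is lost.

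The size of the loss cannot be fixed from the documents. The 14%, 43% and 71% figures for the 12-day search at 6, 8 and 10 nights assume discharge-only coding, the stated stay, evenly spread return days and no recovery by another route. The change is still worth making: the loss depends on length of stay, it enters rates reported to the IDMC, and it is easy to remove.

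**What to change.** 1. In Tables 4 and 6, name the date field, and select candidates by return-visit or admission date within 7 days of the index visit. This loses no case at any length of stay, provided that date is recorded.
2. Where only a discharge-dated code exists, widen the code search, for example to day 30, to match the encounter window in Appendix E. The Hypothesis 4 table there lists CPT codes only, so ICD-10 codes would have to be added. It describes Adate as a diagnosis date and gives Ddate no description, so both need defining before use.
3. Keep the manual 7-day check in Table 4. Add the same check in Table 6, where the present review looks only for delayed care.
4. State how the Table 4 count relates to the EHR, chart and pathology reviews in Section 6(b), and which source decides.

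The cost is a changed date condition in two queries, the ICD-10 addition if the 30-day table is used, and some extra charts for the existing reviewers. In the fallback search, the extra charts are limited to patients with a listed code on days 13 to 30 (Table 4) or days 8 to 30 (Table 6).
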